## Methods/Design

### Design and setting

Ideally, a CRM training should be evaluated in a large multicenter trial [28]. In our case, time and money were limited, thus we looked for an alternative way to control for institutional variation. We chose for a paired controlled trial, with one pre-test and two post test measurements. Three pairs of comparable ICUs were selected out of a predefined cluster of eligible medium sized units (10 to 16 beds and 55 to 88 employees) of non-academic teaching hospitals. This type of ICU was chosen because these are large enough to form an independent unit, yet small enough to train all of the staff. Moreover, most ICUs in the Netherlands belong to this category or aim to accomplish this. Per pair one ICU received the training directly after the pre-test measurement and one ICU served as a control group. The participating hospitals had on average 641 beds and are located in an urban environment.

Data collection took place from November 2009 until May 2010 (pre-test), June 2010 until September 2010 (post-test 1), and in November 2010 until May 2011 (post-test 2). In each measurement period data were simultaneously collected for the intervention and control unit, and consecutively for all pairs. Per pair each measurement period took 7 to 9 weeks. The intervention units received the training directly after the pre-test. The first post measurement was conducted three months after the training and the second post-measurement followed one year after the training.

ICUs that fitted the profile of a possible intervention unit (i.e. hospital type; ICU size, level and staffing; closed format; taking part in the Dutch National Intensive Care Evaluation (NICE) registry [29]) were approached to participate in the present study (*n *= 12). Most of these ICUs were interested in CRM but unable to fulfil financial needs to start within the study period. Four ICUs were willing to act as an intervention unit and able to pass formal barriers, like finance and organisational arrangements. Of these four, one unit served as a pilot unit, and the other three units served as the intervention group in the main study.

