### Observation of non-technical skills

Direct observations were used to determine the use of non-technical skills by the IC staff who had direct contact with patients. To assess non-technical skills, an observational model of the Royal Dutch Airlines was used (i.e. SHAPE) [47], which was adjusted for health care (Explicit Professional Oral Communication measurement (EPOC); development and psychometric results will be published separately).

The EPOC classifies explicit professional oral communication of an observed person into six dimensions; assertiveness, working with others, task-oriented leadership, people-oriented leadership, situational awareness, and planning and anticipation. Each dimension is subdivided into several concrete verbal behaviours that together represent the dimension. Throughout an observation of 30 minutes an independent observer tallies how often each verbalization is displayed by the observed person, e.g. 'asks for input', 'coordinates tasks', or 'expresses concerns'. Only professional interaction with co-workers of the ICU was tallied, so social talk or conversations with the patients or family were not tallied.

All observers had a non-medical background in social sciences and were trained for four days. During this training the observers learned the definitions of the verbal behaviours and practised observing at an ICU. To ensure that all observers rated behaviour in the same way and were consistent over time during the data collection period, regular meetings were organized to discuss complex cases. Additionally, 8% of observations were double coded by two independent observers contemporaneously. Furthermore, a 17 minute video of an ICU nurse was used to check the observers' consistency over time. Blinding observers for intervention status of a unit was not possible. Therefore, medical staff was instructed not to discuss the training or CRM issues with the observers and the observers were kept ignorant of the content of the training.

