### Statistical analyses

The collected data will be checked for completeness and the characteristics and frequency of missing data will be described. Descriptive statistics will be used to describe baseline characteristics of patients, staff and ICU. Comparability of paired intervention and control ICUs will be assessed by comparing baseline data and structural indicators (e.g. number of beds). The effect of the CRM training will be assessed by comparing the before and after measurements of the intervention and control ICUs on all levels of Kirkpatrick's evaluation framework. Changes in patient safety culture, attitude and teamwork behaviour will be described and tested with the ANOVA procedure for repeated measures. This will be done on an individual level with adjustment for the unit. With the observations it is plausible that the different observations within one person will cluster with each other. To control for this clustering, a multilevel analysis will be applied with additional adjustment for the unit. Changes in patient outcomes or incidence of adverse outcomes during the follow-up will be assessed using linear regression analysis while adjusting for case-mix differences and clustering within an ICU.

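### The planned model for the observed behaviour accounts for person and unit but not for observer, so a change in observer mix or strictness between waves could be confounded with the training effect

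*Protocol article*

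**What the plan says.** The section Observation of non-technical skills defines the outcome as a count: "Throughout an observation of 30 minutes an independent observer tallies how often each verbalization is displayed by the observed person". On blinding it states: "Blinding observers for intervention status of a unit was not possible". In mitigation, "medical staff was instructed not to discuss the training or CRM issues with the observers and the observers were kept ignorant of the content", meaning what the CRM sessions taught.

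The same section treats disagreement and drift between observers as matters to be managed. Observers had four days of training. Then: "To ensure that all observers rated behaviour in the same way and were consistent over time during the data collection period, regular meetings were organized". Agreement was also checked directly: "Additionally, 8% of observations were double coded by two independent observers contemporaneously". A 17-minute video was also used to check consistency over time.

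Under Design and setting: "In each measurement period data were simultaneously collected for the intervention and control unit, and consecutively for all pairs". Each measurement period took 7 to 9 weeks per pair. Table 2 places the observations at baseline and at the second follow-up, one year after the training.

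The Statistical analyses section compares before and after measurements in intervention and control ICUs. For the observations it names one source of clustering, repeated observations of one person, and one adjustment, for unit: "To control for this clustering, a multilevel analysis will be applied with additional adjustment for the unit". The article gives neither the number of observers nor their allocation to units and waves.

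**The concern.** The article works to control observer variation when the data are collected, then leaves it out of the model that analyses them. The effect of interest is the change from baseline to second follow-up in the trained units minus the change in the control units. A unit term removes only what stays constant within a unit. If the observers in one unit of a pair changed over that year, or became more or less strict, in a way not matched in the other unit, the resulting difference lies in the unit-by-wave contrast, which is where the training effect is read. Double coding and the video measure agreement, but neither is said to enter the estimate or its standard error.

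At stake is the test on the observed outcome, which the article's concluding remarks list among the three features that set the study apart. If observer variance is present and unmodelled, the interval is too narrow and the test rejects too often.

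**Working it through.** The article gives no sample size, SD or effect size for the observations, so there is no stated figure to reproduce. All numerical inputs below are assumptions, except the three pairs, the two waves and the two observations per person (the article aims for two or three).

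**Step 1. When does an observer difference cancel?** Let observer A tally r times as many behaviours as observer B, with no training effect. If A makes a share s of the observations in a unit and wave, the mean there is proportional to m(s) = s·r + (1 − s). The spurious effect ratio is

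[m(intervention, post) / m(intervention, pre)] ÷ [m(control, post) / m(control, pre)].

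| A's share, pre to post | r = 1.1 | r = 1.2 | r = 1.3 |
|---|---|---|---|
| 50% in both units, both waves | 1.00 | 1.00 | 1.00 |
| 100% intervention, 0% control, both waves | 1.00 | 1.00 | 1.00 |
| 50% to 75% intervention, 50% to 25% control | 1.05 | 1.10 | 1.14 |

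The second row shows that even complete separation of observers by arm does no harm to the before-after contrast if it is the same in both waves. The third row shows that a differential shift does. A simulation with observer omitted (60 persons per arm, 2 observations per period, mean 20 tallies, person SD 0.3 on the log scale, 2000 runs) gave a type I error of about 0.05 in the first two rows. In the third row it was 0.22, 0.58 and 0.83.

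**Step 2. Effect on the standard error.** Assume 30 people with 2 observations each per unit-wave, person SD 35% and residual SD 50% of the mean tally, and different staff in the two waves.

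- Variance of one unit-wave mean: (0.35² + 0.50²/2)/30 = 0.2475/30 = 0.00825.
- The effect averages three pairs, each a contrast of four unit-wave means, so the model's SE = √(4 × 0.00825/3) = 0.105.
- With k observers per unit-wave, sharing its sessions equally and none working anywhere else, and observer SD s, the true SE = √(0.011 + 4s²/(3k)).
- Rejection rate of the nominal 5% test = 2 × [1 − Φ(1.96 × 0.105 / true SE)].

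| Observer SD | True SE, k = 1 | Rejects, k = 1 | True SE, k = 3 | Rejects, k = 3 |
|---|---|---|---|---|
| 0 | 0.105 | 5% | 0.105 | 5% |
| 5% | 0.120 | 9% | 0.110 | 6% |
| 10% | 0.156 | 19% | 0.124 | 10% |
| 15% | 0.202 | 31% | 0.145 | 16% |

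A simulation of the k = 1 case with 4000 replicates agrees: 0.089, 0.194 and 0.304. When the same observers were shared equally over both units of a pair, the simulated rejection rates were 0.049, 0.051 and 0.048.

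**Step 3. Sensitivity.** If the same staff are seen in both waves, person variance cancels. The model's SE becomes √(4 × 0.125/30/3) = 0.075, and rejection at k = 1 becomes about 12%, 29% and 44%.

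**The case against.** The strongest reply is that this is a condensed article. Rostering of observers is a detail it may leave to the full protocol, and it says that the development and psychometric results of the observation instrument will be published separately. That stands as far as allocation goes: silence on rostering is not in itself a fault. It does not cover the model, which the article does state and which names person and unit only.

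A reader might infer from "In each measurement period data were simultaneously collected for the intervention and control unit" that each hospital in a pair had its own observers. The text does not support this. Sessions lasted 30 minutes within a window of 7 to 9 weeks, so one observer could have served both hospitals, and one team could have served all pairs in turn.

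A reader might also infer that an observer who simply tallies more than colleagues would pass for a training effect. In the planned before-after comparison this is wrong, as the second row of the first table shows. The shift has to differ between units and between waves.

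The one-observer-per-unit-wave figures are an upper scenario. Live double coding means that at least two observers were in the same unit wherever it was done, and the training, meetings and video aim to keep observer variance small. More observers per unit-wave, shared observers or returning observers all bring the inflation down.

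Finally, an observer term does nothing about expectation: if observers who know the arm all lean the same way in trained units, balance and modelling leave that bias in place. The article's own safeguards address that risk, and it should be kept apart from this point.

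**Conclusion.** The point holds in a limited form. The stated model omits a source of variation that the article itself recognises, and adjustment for unit cannot remove the part of it that changes between waves. The article shows neither imbalance of observers nor an inflated test; both depend on an allocation it does not report. Under the stated assumptions, the rejection rate of a nominal 5% test runs from about 5% with observers balanced over the pair, through 6% to 16% with three separate observers per unit-wave, to about 9% to 30% with one new observer per unit-wave, for an observer SD of 5% to 15% of the mean. If the same staff were observed twice, the one-observer figures rise to about 12% to 44%. These figures show a mechanism and a range and are not an estimate for this trial. The analysis is still written in the future tense, so the model should be amended before it is run.

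**What to change.** Data collection is described in the past tense, so the change is to the analysis:

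- Tabulate the observations by observer, unit and wave. If observers were balanced within pairs, the table shows it and the concern largely falls away.
- Add observer to the multilevel model, crossed with person. Use a fixed effect if observers are few.
- Use the double-coded 8% and the video scores to gauge the observer variance.
- Report the behavioural effect with and without the observer term.
- Where an observer worked in only one unit of a pair in a wave, state that observer and unit-by-wave cannot be separated there.
- Report expectation bias from unblinded observers as a separate limitation.

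The cost is one table and one more term in a model already planned, provided that observer identity was recorded for each session. The downside is a slightly wider interval for the behavioural effect.

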### Cost-effectiveness analysis

An economic evaluation will be carried out from a societal perspective and according to the Dutch guidelines for costing in economic evaluations [54,55]. The costs of CRM training will be assessed bottom-up, based on personnel time, material, housing and travel costs spend on the training. Direct medical costs of hospital stay will be assessed by multiplying the number of bed days in- and outside ICU with standard cost-prices from a societal perspective. If relevant, costs of extra interventions related to adverse outcomes during ICU stay will be included.

To assess the cost-effectiveness of CRM training compared to no training with regard to patient safety at ICUs, the incremental costs per prevented adverse outcome will be computed. In addition a cost-benefit analysis will be performed to compare incremental costs of training with incremental costs of hospital stay.

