A CRM change team was formed in each trained ICU to stimulate and facilitate the implementation of CRM initiatives after the training had ended. This team consisted of enthused representatives of all the professions and management which. The plans of actions of all the training sessions formed the starting point. Who and how many people exactly joined the change team was different for each ICU. Part of the training is that the two CRM instructors offer their help as consultant for one day or two day parts after the ICU was trained. It was up to the change team how to utilize this help (e.g. get organised; implement changes; reiterate theory).

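### Intervention cost stops at the training, while the measured effect includes the change team and the initiatives that follow it, and the societal label is wider than the items listed

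*Protocol article*

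**What the plan says.** The section on cost-effectiveness analysis in the Protocol article announces that "An economic evaluation will be carried out from a societal perspective" and refers to the Dutch costing guidelines. It then names three cost items:

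- **Training:** built bottom-up, "based on personnel time, material, housing and travel costs spend on the training".
- **Hospital stay:** obtained by "multiplying the number of bed days in- and outside ICU with standard cost-prices from a societal perspective".
- **Adverse outcomes, conditionally:** "If relevant, costs of extra interventions related to adverse outcomes during ICU stay will be included".

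Two results follow. For the first, "the incremental costs per prevented adverse outcome will be computed". The second is a cost-benefit analysis that sets the incremental cost of training against the incremental cost of hospital stay.

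The section on the intervention says that each trained ICU formed a change team to "stimulate and facilitate the implementation of CRM initiatives after the training had ended". It also says that the two instructors' consultancy after the training belongs to the training. The section on interpretation of the results classes CRM as a generic intervention that produces specific ones, with a handover checklist, a white board and a patient-transport protocol as examples.

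**The concern.** A cost-effectiveness ratio is interpretable only if numerator and denominator refer to the same intervention. Here the denominator, adverse outcomes prevented during follow-up, reflects everything that happened in the trained ICUs after the course, including the change team's work and the initiatives it launched. The intervention part of the numerator ends with the course.

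The article describes change teams only for trained ICUs, so their cost falls on the intervention side. If it is left out, the cost per prevented adverse outcome looks lower than it is. In the cost-benefit comparison, any saving in bed days has a smaller outlay to cover. A hospital deciding whether to buy the training would not see the staff time that the authors themselves regard as needed to make it work.

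The perspective raises a second, lesser question. A reader who sees the word societal expects more than training, bed days and in-ICU interventions for adverse outcomes.

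**Working it through.** The article gives no unit cost, no cost ratio, no change-team hours and no expected number of prevented events, so there is no figure to reproduce. The check compares scopes and then gives a rough scale.

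**Scope comparison**

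| Component | Where described | Among the listed costs? |
|---|---|---|
| Two-day course | Intervention section | Yes |
| Instructors' consultancy afterwards | Intervention section, as part of the training | Plausibly, as training cost |
| Change-team time after the training | Pilot study; Intervention section | No |
| Staff time and materials for resulting initiatives | Interpretation of the results | No |
| Bed days in and outside the ICU | Cost-effectiveness analysis | Yes |
| Extra interventions for adverse outcomes during ICU stay | Cost-effectiveness analysis | If relevant |

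Two components that the article treats as the path to the effect have no cost entry. Nor is an instrument described that would supply one. The interviews ask whether and how CRM was implemented, and neither they nor Table 2 mention hours or costs.

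**Effect on the two results**

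Write T for training cost, H for the difference in hospital-stay cost, A for the difference in adverse-outcome intervention cost, I for the extra cost of the change team and initiatives in trained over control units, and E for adverse outcomes prevented.

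- Ratio as described: (T + H + A) / E. With I included: (T + H + A + I) / E. The understatement is I / E.
- Cost-benefit as described: T against H. With I included: T + I against H. The understatement of outlay is I.

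If E and I are both positive, each result is shifted in favour of CRM, other omissions held aside.

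**Scale in staff hours**

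Inputs from the article: two days from 9 to 17 o'clock (Intervention section); 55 to 88 employees per unit (Design and setting); three or four change-team members suggested (Pilot study); follow-up of one year (Design and setting). Assumed, because the article is silent: 1 to 8 hours per member per month.

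- Training per employee: 2 × 8 = 16 h.
- Training per ICU: 55 × 16 = 880 h, to 88 × 16 = 1,408 h.
- Change team, low: 3 × 1 × 12 = 36 h. High: 4 × 8 × 12 = 384 h.
- Smallest share: 36 / 1,408 = 2.6%. Largest share: 384 / 880 = 43.6%.

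These are shares of training hours, not of cost. Material, housing, travel and bed-day costs also enter the incremental cost, so the percentages do not measure the error in the ratio. Staff time for the initiatives would come on top and cannot be derived.

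**The case against.** The strongest reply is that this is a condensed article which cites costing guidelines and does not call its list of items exhaustive. The full list may stand in a document not shown. That carries weight for the perspective: the absence of post-discharge, productivity or informal-care costs from a summary does not prove they will be ignored. It carries less weight for the intervention cost, because there the article states a boundary. It ties the cost to the training and uses training cost again to define the cost-benefit analysis.

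Four further points stand and limit what can be said.

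- A reader might infer that the ratio as a whole is biased in favour of CRM. The article does not support that. If CRM prevents harm, unlisted savings after discharge or in productivity would work against CRM when left out, and the control units' own improvement work is uncosted too.
- A reader might also infer that only training and hospital stay are costed. The conditional third item shows otherwise.
- The instructors' follow-up should not be called omitted, since the article counts it as training.
- Change-team hours are not documented, and team size and composition differed between ICUs, so any percentage depends on the hours assumed.

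It can also be said that the cost-benefit comparison declares its scope openly. It does, but an openly stated scope can still be narrower than the intervention whose effects are measured.

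**Conclusion.** The point holds in a limited form. Followed as written, the plan credits CRM with one-year effects that run through the change team and its initiatives, but charges it only for the training. Taken alone, that understates CRM's incremental cost in both economic analyses, provided control units did not carry out comparable uncosted work. The amount is unknown; about 3% to 44% of training hours is an illustration under assumed hours, covers the change team only, and is not an estimate of the error in the ratio. The net direction once all unlisted societal costs are considered cannot be settled from the article. Separately, the declared perspective is wider than the three items listed, and the two should be brought into line. The trial design and the effectiveness analyses are not affected.

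**What to change.** Reconcile the cost-effectiveness section with the sections on the pilot, the intervention and the interpretation of results:

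- Define intervention cost as the training, including the instructors' consultancy, plus change-team hours and the staff time and materials of resulting initiatives over the follow-up year.
- Take these inputs from unit records or from retrospective estimates by the change teams. The one-year interview cannot be relied on alone: the article reports it in the past tense, and one chairman's recall is a weak source for a year of unit-wide hours.
- Where data are lacking, report a sensitivity analysis over a stated range of hours.
- Use the same definition in the cost-benefit analysis.
- Name the perspective after the items actually costed (hospital or health-care) unless wider societal costs are included.

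The price is a little more data work and a cost ratio that may be somewhat less favourable.
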